
#### Exclusion criteria

2.3.2

Distant metastases (the following populations are excluded: stage IVc HPV-negative HNSCC and SGC, stage IV p16-positive oropharyngeal squamous cell carcinoma, stage IVb NPC).Thyroid cancers, non-melanoma skin cancers (e.g. squamous cell carcinoma of the skin, skin basal cell carcinoma, skin adnexal carcinoma), and non-carcinoma HNC (e.g. melanoma, sarcoma, etc.) are excluded.Subjects with previous malignancies (except localized non-melanoma skin cancers, and the following *in situ* cancers: bladder, gastric, colon, esophageal, endometrial, cervical/dysplasia, melanoma, or breast) unless a complete remission was achieved at least 5 years prior to study entry AND no additional therapy is required during the study period. Premalignant lesions (e.g., leukoplakia, erythroplakia, lichen etc.) are allowed.Participation in clinical trials with other experimental agents within 30 days of study entry or concomitant treatment with experimental drugs.Patients unable to comply with the protocol, in the opinion of the investigator.Any known or underlying medical conditions that, in the opinion of the investigator, could adversely affect the ability of the participating subject to comply with the study.Having a smartphone operating system other than Android.

### Instruments

2.4

#### Questionnaires

2.4.1

The EORTC QLQ-C30 is composed of both multi-item scales, including functional scales, symptom scales, a global health status/QoL scale, and single-item measures. Each of the multi-item scales includes a different set of items. Each item is represented once in each scale, meaning that no item occurs in more than one scale (24).

All scales and single-item measures range in score from 0 to 100. A high scale score represents a higher response level. Thus, a high score for a functional scale represents a high/healthy level of functioning, a high score for the global health status/QoL represents a high QoL, but a high score for a symptom scale/item represents a high level of symptoms/problems.

The principle for scales scoring is the same:

Estimate the average of the items that contribute to the scale (raw score).Use a linear transformation to standardize the raw score (ranging from 0 to 100); a higher score in the function scales represents a higher (“better”) level of functioning, or a higher score in the symptom scales a higher (“worse”) level of symptoms.

The EORTC QLQ-HN43 (an update of QLQ-H&N35) is meant for use in head and neck cancer patient populations varying in disease stage and treatment modality (i.e. surgery, chemotherapy and radiotherapy). It should always be complemented by the EORTC QLQ-C30. As described for EORTC QLQ-C30, all scales and single-item measures of EORTC QLQ-HN43 range in score from 0 to 100.

The EQ-5D-5L is a standardized measure of health status developed by the EuroQol Group in order to provide a simple, generic measure of health for clinical and economic appraisal (25).

The EQ-5D-5L consists of the EQ-5D-5L descriptive system and the EQ Visual Analogue Scale (EQ VAS). The descriptive system comprises five dimensions (mobility, self-care, usual activities, pain/discomfort, anxiety/depression). Each dimension has five levels: no problems, slight problems, moderate problems, severe problems, and extreme problems. The respondent is asked to indicate his/her health state by ticking (or placing a cross) in the box against the most appropriate statement in each of the five dimensions. This decision results in a 1-digit number expressing the level selected for that dimension. The digits for 5 dimensions can be combined in a 5-digit number describing the respondent’s health state. It should be noted that the numerals 1-5 have no arithmetic properties and should not be used as an ordinal score. The EQ VAS records the respondent’s self-rated health on a 20 cm vertical visual analog scale with endpoints labeled ‘the best health you can imagine’ and ‘the worst health you can imagine’. This information can be used as a quantitative measure of health as judged by the individual respondents (26).

The Cancer Behavior Inventory - Brief (CBI-B) was developed as a measure of self-efficacy strategies for coping with cancer, based on self-regulation and self-efficacy theories (11). It consists of 12 items (rated 1 = not at all confident to 7 = totally confident) and was derived from the longer version of the Cancer Behavior Inventory (CBI) (10, 27). The CBI-B represents a comprehensive and valid brief measure of self-efficacy for coping with cancer that could be easily used as a PROM. It has a consistent factor structure across several types of cancer and established good psychometric qualities (28). The CBI-B total score can be computed by averaging single item scores through arithmetic mean and, thus, ranges in value from 1 to 7.

#### BD4QoL platform

2.4.2

In the BD4QoL project, the opportunities linked to mobile-health (mHealth) and digital phenotyping (29) will be used to continuously monitor QoL trajectories in HNC patients and to detect early related events that need further attention from patients, clinicians, or both.

The BD4QoL platform consists of a set of services to allow patient monitoring and empowerment through two main tools: a Point of Care (PoC) web application to manage all patients’ data and follow-up by clinical investigators, and a mobile application (App) installed on participating subject’s smartphone. Also, a web-form tool is delivered to allow the QoL questionnaire completion.

A preliminary feasibility and users acceptability assessment has been performed at the Istituto Nazionale dei Tumori in Milan, Italy (unpublished, data not shown). This preliminary survey has outlined the preferences of users in terms of mobile technologies to be adopted (mobile phones preferred as compared to home and wearable sensors/devices). Moreover, a pilot study was performed on healthy volunteers to measure the accuracy, precision, and uniformity of data collected by the different mobile phones used by the study participants. The acceptability and usability of the platform were assessed as well within the same preliminary pilot study (data not shown).

To achieve the study objectives, the BD4QoL platform will collect the following data which will be used to identify behavioral and affective traits associated with study outcomes.

Sensors in mobile phones will provide the following readings (further details in **Supplementary Material**):

Accelerometer (x,y,z measurements).Global Positioning System - GPS (Lat, Long).Ambient light (measurement of light in the room/area where the mobile device is located).Screen (Status ON or OFF for smartphone device screen).Activity (type of activity with which the person engages, which can be one of these: Still, Walking, Running, On_Bicycle, In_Vehicle)Daily connections to wifi networks (naming of wifi connections as well as corresponding duration).

The following data are detected from the mobile device’s operating system:

Phone usage logs (total count and timestamps of three types of events – incoming, outgoing and missed calls – with encrypted [that is hashed] collection of associated personal identifiable information, as well as total count and timestamps of incoming and outgoing/replied text messages).Phone applications usage (identification and seconds or minutes of total and detailed usage of any smartphone applications the study participant is using; for certain specific social media network or communication mobile apps, more specific information, that is as duration of app usage per day, is collected based on participant’s permissions; these social applications include Facebook, Messenger, Whatsapp, Telegram, Viber, Zoom, Instagram; no information about the people with whom communication is made nor the content of the communication is collected).

The following data are collected from external datasets:

Steps (daily and per hour number of steps completed through connection to external dataset from Google Fit cloud).Identification of places (Points of Interest) visited, based on participant’s permissions, through the correlation of one’s GPS signal (per day and minute) with external datasets from Foursquare and OpenStreet maps.

The above data will be used to infer activities and behaviors which have a high likelihood of being meaningfully related to participants’ QoL trajectories. A list of such activities and behaviors, with an indication of the technical methods to be used for reconstruction as well as an assessment of reliability, is presented in **Supplementary Material**.

The BD4QoL App, available for Android (**Figure 2**), as listed above, will be able to collect and store information about the following domains: mobility, physical activity, activities of daily living, instrumental activities of daily living, socialization, cognitive function, health-related activities as well as personal affective data (further details in **Supplementary Material**). A summary of the findings and the supporting data will be available to the patient and clinical investigators (e.g., physicians, nurses), through a dashboard available on mobile devices for patients and through the PoC web application for clinical investigators. The data collected by the mobile App will not be available to the technology manufacturer and will be transferred in quasi-real-time (i.e., as soon as a connection for data transfer is available) to the central BD4QoL repository.

**Figure 2 f2:**
[figure not shown]
Screenshot of the BD4QoL study mobile app: **(A)** homepage, **(B)** notification dashboard, **(C)** monthly statistics of step count, **(D)** example of BiDi chatbot conversation.

In the interval between visits, study participants, allocated in the intervention arm, will be able to interact electronically with a chatbot(implementation based on IBM Watson technology), which will be part of the BD4QoL App. The chatbot is an application based on a conversational user interface (30) to empower patients to manage their QoL and health under the supervision of clinical investigators. The chatbot will have a series of electronic coaching (e-coaching) functions that include: (i) dialogue management that allows the patient to be counseled by chatting electronically in a structured and effective way; (ii) management of two-way communications with healthcare professionals [e.g., for the patient to request specific support in case of special needs, or for the chatbot to invite the patient for a visit in case of an early detection of health-related QoL (HRQoL) deterioration or health issues; identified people will have to be listed on the delegation log by the Principal Investigator (PI)]; (iii) detection of affective traits embodied in the e-coach/patient dialogue, through sentiment analysis and emotion analysis technologies to infer information about the participant mood (details about data privacy are reported in the specific section of this protocol). The latter element can be used to both re-adapt the chatbot counseling strategy as well as to provide additional information on the subject’s mood to clinical investigators. The adverse events that the chatbot will be able to recognize will be the following: fatigue, malaise, fever, excessive sleepiness, difficulty sleeping, depression, change in social circumstances, neck swelling, facial pain, difficulty breathing, nose bleeds, difficulty speaking, dry mouth, tooth loss, muscle weakness, ear pain, difficulty hearing, tinnitus, vertigo, nausea, diarrhea, constipation, difficulty seeing, dry eye, eye pain, nervous eyelid, eye floaters, swollen eye, bleeding eyes, eye-watering, sexuality issues, weight loss, difficulty swallowing, mouth sores, appetite loss, difficulty opening mouth, difficulty eating, increased sensitivity to smells, no taste. Further details about adverse events and potential chatbot responses are reported in **Supplementary Table 2**.

The platform will provide the investigators with real-time data on device usage (e.g., number and type of alerts and chatbot interactions by pts), and it will integrate the electronic case report forms (eCRF) as a study monitoring dashboard through the PoC web application.

The BD4QoL platform used in this trial is not to be considered a medical device and is used for experimental assessment only. No drugs will be suggested by the automated chatbot responses. Tips provided by the chatbot regarding detected symptoms are also not to be considered clinical advice by any means and should not be a substitute for conversations with a member of trained medical personnel. A relevant disclaimer in this sense is also clearly shown by the chatbot itself to the study participant.

### Sample size calculation and statistical plan

2.5

#### Sample size

2.5.1

The primary endpoint is the proportion of HNC survivors experiencing a clinically relevant deterioration in global health-related QoL as previously defined.

In the European BD2Decide project (31), funded by the Horizon 2020 program and concluded in November 2019, the analysis of QoL questionnaires was performed on over 450 stage III-IV HNSCC patients (recruited from Italy, Germany, and the Netherlands; data cut-off date 23^rd^ September 2019): at least two consecutive EORTC QLQ-C30 questionnaires filled in after at least 6 months of follow-up were available for 117 patients; among them, a clinically meaningful deterioration of QoL (reduction of at least 10 points) was observed in 22 (19%) cases during post-curative treatment follow-up.

The second historical cohort comprised 65 patients from Mainz (Germany) having EORTC QLQ-C30 questionnaires completed 24 and 36 months after curative surgery (32). In this population, the percentage of subjects experiencing a deterioration ≥ 10 points in EORTC QLQ-C30 global health status from the 24^th^ to the 36^th^ months after treatments was 23%.

In the Head and Neck 5000 project (UK) (33) repeated global health scores at 12 and 36 months after treatment were available for 1241 people with HNC. A clinically meaningful deterioration of QoL (reduction of at least 10 points) was observed in 18% of these subjects.

In these three existing studies, the average percentage (arithmetic mean) of HNC patients experiencing a clinically meaningful deterioration of EORTC QLQ-C30 global score (reduction of at least 10 points) during follow-up was 20% (19% BD2Decide, 23% Mainz, 18% HN5000). These findings are preliminary and will be explored further as part of the European Union (EU) program supporting this study.

The primary endpoint of this study is the proportion of patients showing a reduction of at least 10 points in EORTC QLQ-C30 global health status score in HNC survivors. Therefore, considering the null hypothesis (*H_0_
*) of no difference for the primary endpoint, the proportion of HNC survivors showing a reduction of at least 10 points in EORTC QLQ-C30 global health status during 24-month FU in the control group is 20% (*µ_0_
*), as derived from the historical benchmark data.

Considering the alternative hypothesis (*H_1_
*), the desired proportion of HNC survivors showing a reduction of at least 10 points in EORTC QLQ-C30 global health status during FU in the intervention group is 10% (*µ_1_
*).

The minimal clinically relevant difference (*δ*) [superiority randomized controlled trials (RCTs)] between the null hypothesis (*H_0_
*) of no difference and the alternative hypothesis (*H_1_
*) is 10%. We fixed the significance level (*α* = 0.05, one-tailed) and the power (*1-β* = 0.80, at least). It has been calculated a group sample sizes of 112 subjects (the control group) and 224 subjects (the intervention group) will result in 80% power (*1-β*) to detect a difference of 10% between the null hypothesis (*H_0_
*) that both group proportions are 20% and the alternative hypothesis (*H_1_
*) that the proportion in group under study is 10%, using a one-sided chi-squared test (*χ*
^2^ test) (Mantel-Haenszel test) and with a significance level of 0.05 (*α*, one-tailed) (PASS Sample Size 2020 statistical software).

With a supposed drop-out of 20%, it has been calculated a group sample size of 140 subjects (the control group) and 280 subjects (the intervention group), for a total cohort of 420 participants.

The data will be published in clinicaltrials.gov and will be reported to study PIs and to the Funding Authority. The protocol writing committee will have the final decision regarding study termination.

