## Abstract

Patients surviving head and neck cancer (HNC) suffer from high physical, psychological, and socioeconomic burdens. Achieving cancer-free survival with an optimal quality of life (QoL) is the primary goal for HNC patient management. So, maintaining lifelong surveillance is critical. An ambitious goal would be to carry this out through the advanced analysis of environmental, emotional, and behavioral data unobtrusively collected from mobile devices. The aim of this clinical trial is to reduce, with non-invasive tools (i.e., patients’ mobile devices), the proportion of HNC survivors (i.e., having completed their curative treatment from 3 months to 10 years) experiencing a clinically relevant reduction in QoL during follow-up. The Big Data for Quality of Life (BD4QoL) study is an international, multicenter, randomized (2:1), open-label trial. The primary endpoint is a clinically relevant global health-related EORTC QLQ-C30 QoL deterioration (decrease ≥10 points) at any point during 24 months post-treatment follow-up. The target sample size is 420 patients. Patients will be randomized to be followed up using the BD4QoL platform or per standard clinical practice. The BD4QoL platform includes a set of services to allow patients monitoring and empowerment through two main tools: a mobile application installed on participants’ smartphones, that includes a chatbot for e-coaching, and the Point of Care dashboard, to let the investigators manage patients data. In both arms, participants will be asked to complete QoL questionnaires at study entry and once every 6 months, and will undergo post-treatment follow up as per clinical practice. Patients randomized to the intervention arm (n=280) will receive access to the BD4QoL platform, those in the control arm (n=140) will not. Eligibility criteria include completing curative treatments for non-metastatic HNC and the use of an Android-based smartphone. Patients undergoing active treatments or with synchronous cancers are excluded.

Clinical Trial Registration: ClinicalTrials.gov, identifier (NCT05315570).

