**Figure 1 f1:**
[figure not shown]
Study design of the randomized controlled trial.

In this scenario, the 2:1 ratio was chosen for the following reasons: i) the study devices are deemed to be safe and able to provide timely monitoring of participants health status, thus 1) possibly improving their condition as compared to the control group and 2) minimizing the number of patients not exposed to this potential benefit; ii) the platform acts unobtrusively, and it favors contact with healthcare professional which is normally very well accepted and pursued by patients; moreover it is designed to allow for patients’ empowerment; iii) we anticipate that costs associated with SoC not supported with the BD4QoL platform will be superior because subjects randomized in the intervention arm are deemed to experience less adverse events than controls. In this context, a cost-effectiveness analysis is planned as an exploratory endpoint (**Table 2**).

As stated by Palmer et al., favoring the experimental therapy is warranted in trials of potentially significant public health benefit (21). Unequal allocation schemes can improve recruitment and partially satisfy the individual ethics criterion (the study participants have a higher probability of being randomized in the intervention arm than in control one). They can also be useful if widespread knowledge about the control therapy already exists and if more understanding is desired about the new treatment.

The randomization procedure will be web-based, centralized, computerized (software-generated randomization list using RedCap web-based platform) (22, 23). Local research teams will be blinded to the randomization list (local people designated to the randomization procedure will not know the randomization list, but clinical investigators will not be blinded to the outcome of the randomization). The biostatistician doing the analysis of the trial will be blinded to the list as well until the statistical analysis plan, previously defined, is signed.

The EORTC QLQ-C30 (4), EORTC QLQ-HN43 (6), EQ-5D-5L (8), and CBI-B (11) evaluations will be performed at 0-, 6-, 12-, 18-, 24-month from randomization. The time zero is considered to be the date of randomization. The scores of the EORTC QLQ instruments [as defined in (13, 14)] will be compared to the respective scores of the previous study time-point.

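### The 20% control rate comes largely from single before/after pairs and does not estimate an endpoint with up to four comparisons, so the stated 80% power is not supported for that endpoint

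*Protocol article*

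**What the plan says.** **Endpoint.** The Abstract defines the event as a global health deterioration ("decrease ≥10 points) at any point during 24 months post-treatment follow-up"). Section 2.2 schedules questionnaires at 0, 6, 12, 18 and 24 months and says that scores "will be compared to the respective scores of the previous study time-point". Section 2.6.7 makes the first such drop between questionnaires 6 months apart the primary-endpoint event and ends participation there. A patient who stays in the study therefore has up to four comparisons at which to become an event.

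**Planning rate.** Section 2.5.1 averages three sources:

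- BD2Decide: 22 of 117 patients (19%), each with at least two consecutive questionnaires. The number of pairs per patient is not given.
- Mainz: 23% of 65 patients, month 24 against month 36.
- Head and Neck 5000: 18%, where "repeated global health scores at 12 and 36 months after treatment were available for 1241 people with HNC".

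The mean is then used as the control-arm rate over the whole follow-up: "global health status during 24-month FU in the control group is 20" per cent.

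**Sample size.** Section 2.5.1 states that "group sample sizes of 112 subjects (the control group) and 224 subjects (the intervention group) will result in 80% power" "to detect a difference of 10% between the null hypothesis" (20% in both arms) and the alternative of 10% in the intervention arm, "using a one-sided chi-squared test" "and with a significance level of 0.05". Allowing for 20% drop-out gives 140 + 280 = 420.

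**The concern.** The planning rate and the endpoint are different quantities, and they differ in two opposing ways.

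- **Fewer comparisons.** A single pair taken 12 or 24 months apart gives each patient one chance of an event and misses a dip that recovers in between. The trial counts such dips.
- **Longer gaps.** A slow decline of less than 10 points per 6 months can show up over a 24-month pair and yet never trigger the visit-to-visit rule.

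Section 2.5.1 adjusts for neither. The control rate drives the power for the primary endpoint and is the basis for N = 420. If the rate under the trial's rule is well above 20%, power for the 10-point difference named in the plan is well below 80%, and a null result would be hard to interpret.

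**Working it through.** **1. The plan's own figure.** Inputs from section 2.5.1: p0 = 0.20, p1 = 0.10, 112 control, 224 intervention, one-sided alpha 0.05.

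Power = Φ{[(p0 − p1) − 1.645·s0] / s1}, with s0 = √[p̄(1 − p̄)(1/112 + 1/224)] and s1 = √[p0(1 − p0)/112 + p1(1 − p1)/224].

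- p̄ = (112 × 0.20 + 224 × 0.10)/336 = 0.1333; s0 = 0.03934; s1 = 0.04278.
- (0.10 − 1.645 × 0.03934)/0.04278 = 0.825, so power = 79.5%.
- Exact binomial enumeration of the one-sided Mantel-Haenszel test gives 80.1%.
- Drop-out: 112/0.80 = 140 and 224/0.80 = 280.

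The plan's arithmetic reproduces. Only the input is in question.

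**2. Where the 20% comes from.** (19 + 23 + 18)/3 = 20.0%. The two explicit single-pair cohorts hold 65 + 1241 = 1306 of 1423 patients, and their unweighted mean is (23 + 18)/2 = 20.5%. The figure therefore does not depend on BD2Decide.

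**3. What the rate could be under the trial's rule.** The document gives no within-patient correlation, so each line is an assumption. Changes are taken as normal with mean zero. In the random walk, the SD of change grows with the square root of time.

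| Assumption | SD of 6-month change | Rate per comparison | Any of four |
|---|---|---|---|
| Random walk, 18% over 24 months | 10.92 × √(6/24) = 5.46 | 3.4% | 13% |
| Random walk, 20% over 24 months | 11.88 × √(6/24) = 5.94 | 4.6% | 17% |
| Random walk, 23% over 12 months | 13.53 × √(6/12) = 9.57 | 14.8% | 47% |
| Four independent comparisons at 20% | – | 20% | 1 − 0.8⁴ = 59% |
| Stable score plus independent visit noise, 20% per pair (simulated) | 11.88 | 20% | 66% |

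The starting SDs are 10/z: 10/0.915 = 10.92, 10/0.842 = 11.88 and 10/0.739 = 13.53. The random-walk entries are 1 − (1 − q)⁴, with q the rate per comparison. Patients who contribute fewer comparisons have fewer chances: at an independent 20% each, two give 1 − 0.8² = 36% and three give 1 − 0.8³ = 49%.

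**4. Power of 112/224 across control rates.** Same formula, one-sided 0.05, with exact values in brackets.

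| Control rate | Absolute 10-point difference | Halving of the rate |
|---|---|---|
| 13% | 94% (96%) | 63% (62%) |
| 20% | 79.5% (80.1%) | same |
| 25% | 71% (71%) | 88% |
| 30% | 65% (65%) | 93% (94%) |
| 40% | 57% (57%) | 98.5% (98.6%) |
| 50% | 54% (53%) | over 99% |
| 59% | 53% (53%) | over 99% |

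Worked line at 30% against 20%: p̄ = 0.2333, s0 = 0.04895, s1 = 0.05089, and (0.10 − 0.08052)/0.05089 = 0.383, so power = 65%.

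The difference detectable with 80% power (normal approximation) is about 12.1 points at a 30% control rate, 13.4 at 40% and 14.2 at 50%.

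**The case against.** **Direction.** The range of 13% to 66% straddles 20%. A 6-month gap may produce fewer 10-point drops than a 12- or 24-month gap, and a random walk calibrated to 20% over 24 months gives 17%, close to the plan. This stands. A reader might infer that the trial is underpowered, or that the true rate is near 59%. The document supports neither. The pattern of 23% over 12 months against 18% over 24 months looks more like noise than drift, but 23% of 65 patients has an exact 95% interval of about 14–35%, from a different cohort with a different starting point, so it is only suggestive.

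**Effect scale.** If the intervention halves whatever the control rate turns out to be, a higher rate raises power. This also stands, and the halving column has to be shown. It does not rescue the stated 80%, because section 2.5.1 fixes the minimal clinically relevant difference as an absolute 10%.

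**The third source.** BD2Decide may include patients with several pairs, in which case its 19% could be nearer to an any-visit rate. It would be too strong to say that all three benchmarks are single pairs. But the document does not give the number of pairs, and the other two sources yield 20.5% on their own.

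**Already acknowledged.** Section 2.5.1 calls the historical findings preliminary and says that they will be explored further. That helps the remedy, but the 80% is still stated without qualification.

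**Conclusion.** The point holds as a mismatch between the planning rate and the endpoint. The 20% does not estimate the proportion with a drop against the previous visit at any of up to four 6-monthly comparisons, so 80% power is not supported for that endpoint. For the stated 10-point difference, power is 65% at a 30% control rate and about 53% at 50–59%. It exceeds 80% if the rate is below 20%. These figures assume 112/224 evaluable patients and the planned one-sided test at 0.05. The rates themselves rest on the assumed models above.

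Two stronger readings fail. It is not a calculation error, since the plan's numbers reproduce. Nor is the target difference left undefined, since section 2.5.1 gives 20% against 10% and names the absolute difference.

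Severity: should-fix, as a planning assumption.

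**What to change.** In section 2.5.1:

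1. Re-derive the control rate under the trial's own rule (any drop of at least 10 points against the previous visit, 6-monthly, over 24 months) from historical patients with more than two questionnaires. As described, only BD2Decide might supply them, and the document does not say how many of its 117 patients qualify. If too few do, state the assumed range and the model behind it.
2. Replace the single 80% figure with the power of 112/224 across that range for the stated absolute 10-point difference, and show the halving scenario alongside.
3. Keep N = 420.

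The cost is one re-analysis, where the data allow it, and a rewritten paragraph with a short table. No extra patients are needed and the primary analysis does not change. The downside is that the stated power may become less favourable.
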